## Abstract

**Background:**

Myopia is an escalating global health issue, particularly among adolescents, and its increasing prevalence is associated with a rising burden of ocular complications that adversely affect quality of life and strain healthcare resources. Extensive evidence links prolonged near work to myopia progression, prompting the development of innovative control strategies. One promising approach is the distant-image screen (DIST), which transforms a nearby real image into a virtual one that appears much farther away, thereby reducing the accommodative stress typically induced by prolonged near work. This study is designed to evaluate the efficacy of DIST in delaying the onset of myopia among pre-myopic children.

**Methods:**

This is a 1-year, multi-arm randomized controlled trial involving 192 children, who will be randomly assigned in a 1:1:1 ratio to one of three groups: (1) a DIST group; (2) a Combined Intervention group, which will receive both DIST and an optical defocusing intervention; and (3) a control group, engaging in regular near work without the use of DIST. The primary objective is to assess whether the use of DIST—alone or in combination with optical defocusing—can effectively delay the onset of myopia in pre-myopic children. The primary outcome is the proportion of myopia onset, and the secondary outcomes are the proportion of fast myopia progressors, change in spherical equivalent progression, and change in axial length at each follow-up point.

**Discussion:**

The study aims to determine the independent efficacy of DIST as well as its potential synergistic benefits when combined with optical defocusing techniques. In the context of increasing academic demands and near work exposure, DIST offers a space-efficient, practical solution that could alleviate visual strain without interfering with learning. By providing robust data on both refractive and ocular structural changes, the findings may inform personalized myopia prevention strategies. If successful, DIST could serve as a valuable adjunct to current myopia control methods, ultimately reducing the public health burden of myopia.

**Trial registration:**

Chinese Clinical Trial Registry (ChiCTR), ChiCTR2400082078. Registered on 20 March 2024. https://www.chictr.org.cn/showproj.html?proj=221835.

## Administrative information

Note: the numbers in curly brackets in this protocol refer to SPIRIT checklist item numbers. The order of the items has been modified to group similar items (see http://www.equator-network.org/reporting-guidelines/spirit-2013-statement-defining-standard-protocol-items-for-clinical-trials/).

## Introduction

### Background and rationale {6a}

Myopia is a prevalent refractive error that significantly contributes to visual impairment worldwide. Over the past few decades, the global prevalence of myopia has risen sharply, with epidemiological studies predicting that by 2050, nearly half of the world’s population (approximately 4.758 billion individuals) will be myopic, including almost 1 billion affected by high myopia [1]. The high prevalence of myopia, especially among adolescents in certain populations (80–90%), has reached alarming levels [2, 3]. Myopia has raised considerable public health concerns due to its associated risk of severe ocular complications, such as cataracts, glaucoma, and retinal detachment [4–7]. These complications not only impair vision but also impose a substantial burden on patients’ quality of life and healthcare systems [8, 9]. Moreover, myopia can adversely impact children’s and adolescents’ learning and daily lives, potentially leading to reduced self-esteem and social difficulties [10–12]. Consequently, the prevention and control of myopia have emerged as pressing global public health priorities.

A growing body of evidence highlights the association between prolonged near work—such as reading or engaging in close-up tasks—and the onset and progression of myopia in children and adolescents [13–17]. Mechanistically, near work has been linked to alterations in choroidal thickness, a biomarker increasingly studied in the context of myopia development [18], suggesting that reducing near work exposure could mitigate myopia progression [19]. Furthermore, the extended duration of near work has been shown to have an impact. This understanding has driven the innovation of novel technologies aimed at addressing the challenges of near work.

The distant-image screen technology (DIST) is a novel myopia prevention and control approach developed in the past 2 years. DIST utilizes the “Birdbath” optical design principle and freeform mirror technology to project near scenes to a perceived distance beyond 3 m. This innovation theoretically reduces the visual strain associated with near work while allowing children and adolescents to engage in tasks such as reading and note-taking. A previous clinical study has confirmed that using the DIST for reading does not compromise reading efficiency or increase visual fatigue, providing early support for its feasibility and safety in daily use [20].

In parallel, optical defocus has been widely recognized as an effective strategy for myopia control, with clinical applications such as peripheral defocus glasses and contact lenses [21–24]. While the potential synergistic effects of DIST and optical defocus technologies remain unexplored, their combination may represent a promising avenue for enhancing myopia control outcomes. This research aims to investigate whether DIST and integrating DIST with optical defocus principles can further optimize myopia prevention strategies, offering new insights into evidence-based myopia management.

### Objectives {7}

Based on the aforementioned theories, our primary objective was to evaluate the efficacy of DIST and integrating DIST with optical defocus principles on delaying the onset of myopia, specifically in postponing the initial diagnosis of myopia in pre-myopic children. Additionally, we aimed to determine its impact on mitigating myopic refractive shift and slowing ocular axis elongation. We hypothesized that the DIST intervention would demonstrate superior efficacy in these outcomes compared to the control group, highlighting its potential as a targeted strategy for myopia prevention.

### Trial design {8}

This study will be a randomized, superiority-controlled trial with a parallel-group design. One hundred ninety-two pre-myopic children will be randomly divided into three groups of 64 subjects in a 1:1:1 ratio. The three groups are no use of DIST, DIST alone (RIO-Max 2.0), and DIST optimized by combining the optical defocusing technique (RIO-Ultra 2.0). The complete study flowchart is shown in the figure (Fig. 1). The protocol and all study procedures are approved by the Medical Ethics Committee of the Affiliated Eye Hospital of Wenzhou Medical University (2024–016-K-015–05) and conducted following the ethical standards of the Declaration of Helsinki. The protocol has been registered with the Chinese Clinical Trial Registry (ChiCTR2400082078) and uses the SPIRIT reporting guidelines [25]. Subjects are required to sign an ethical informed consent form before participating in the experiment.

**Fig. 1 Fig1:**
[figure not shown]
The flowchart of the study

## Methods: participants, interventions, and outcomes

### Study setting {9}

Participants in this study will be recruited from the Eye Hospital of Wenzhou Medical University. Screening and baseline examinations will be conducted in the outpatient clinic of the Eye Hospital, using advanced and comprehensive equipment to ensure accurate and complete data collection. Participants assigned to the two intervention groups using DIST will take the devices home. Follow-up supervision will be conducted by the researchers to ensure adherence to the study protocol and proper implementation of the intervention.

### Eligibility criteria {10}

All subjects will undergo initial screening by ophthalmologists and investigators before enrollment. This screening will include inquiries about general health condition, family and disease history, allergies, and current medications. Potential subjects who meet these preliminary criteria will then be further assessed for ocular health and lifestyle habits based on the established inclusion and exclusion criteria.

Inclusion criteria are as follows:Age: 6–10 years old;Spherical equivalent (SE) in either eye: >  − 0.50D and ≤  + 0.75D (based on the average value of automatic refraction under cycloplegia);Astigmatism in either eye: ≤ 1.50D;At least 1 h of near work every day, including non-learning (TV, games, etc.); learning (online learning, punching in); and reading;The uncorrected visual acuity in either eye: ≥ 4.9, and the best corrected visual acuity: ≥ 5.0;Never participated in any clinical trial of myopia control within 3 months or used myopia prevention methods, such as multi-point design defocus glasses, low concentration atropine, repeated low-level red light (RLRL), etc.No manifest strabismus was observed.

Exclusion criteria as follows:Failure to comply with the protocol to obtain reliable study measurements.There is an eye disease that can affect refractive development, such as retinal disease, cataract, and ptosis;The existence of systemic or neurodevelopmental conditions that may affect refractive development;Eye or systemic drugs known to affect the development of myopia or visual acuity through effects on retinal regulation amplitude or intraocular pressure are being used.

### Who will take informed consent? {26a}

Each investigator will personally explain the informed consent form in detail to the subject and their guardian during the recruitment process. This includes providing clear information about the study’s purpose, procedures, potential risks, and benefits, and ensuring sufficient time for them to ask questions and consider their participation. No examinations or interventions will proceed until both the subject and their guardian have provided written informed consent. For children under the age of 8, the guardian will provide consent on their behalf, while verbal assent from the child will be sought whenever appropriate, in accordance with ethical guidelines.

### Additional consent provisions for collection and use of participant data and biological specimens {26b}

N/A: This study does not involve additional data and biospecimens that require subjects’ consent to be collected.

## Interventions

### Explanation for the choice of comparators {6b}

The choice of comparators in this study was guided by the need to evaluate the efficacy of long-term use of DIST and its potential enhancement when combined with the optical defocusing technique in delaying the onset of myopia. This group (daily near work without DIST) serves as the baseline comparator, reflecting typical daily activities that involve prolonged near work without specific interventions. Prolonged near work is a well-documented risk factor for myopia development, but its role in the absence of compensatory measures, such as DIST, remains an important baseline for understanding the natural progression of myopia onset. This control group enables the evaluation of whether DIST alone provides a protective effect against myopia development. By maintaining their habitual near work activities, participants in this group help establish a reference for comparing the effectiveness of interventions.

### Intervention description {11a}

There are two intervention groups in our study: the DIST Group (use of DIST alone) and the Combined Intervention Group (DIST and Optical Defocusing Technique). Participants in these two groups will be asked to use the device during near work, including online learning, playing online games, reading, and similar tasks, with a minimum daily usage of 1 h.

The DIST group is included to investigate whether projecting near scenes into the distance can effectively delay the onset of myopia. This group is critical for isolating the specific effect of DIST as a standalone intervention, independent of other factors. The use of DIST aligns with emerging evidence suggesting that increasing outdoor-like visual experiences or reducing accommodative stress may mitigate myopia progression.

The Combined Intervention group (DIST and Optical Defocusing Technique) evaluates the synergistic effect of combining DIST with an optical defocusing technique. DIST and the optical defocusing technique can be integrated simultaneously through the optical path system (Fig. 2). The system contains two Liquid Crystal Display (LCD) screens, one of which is used to achieve distant-image display, while the other is used to achieve defocus intervention. LCD-1 functions as the object for the distant-image display, while half-mirror-2, the curved mirror, and the lens together form a convex lens optical system. Based on the principles of geometric optics, LCD-1 is positioned within one focal length of this convex lens system. As a result, the light rays entering the eye are divergent, forming an erect, magnified virtual image that enables the perception of a distant image. Similarly, LCD-2 acts as the object for the defocusing pathway, while half-mirror-1, half-mirror-2, and the curved mirror collectively form a convex lens optical system. By positioning LCD-2 between one and two focal lengths of the convex lens optical system, the light rays entering the eye become convergent, thereby achieving defocusing intervention.

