### Relevant concomitant care permitted or prohibited during the trial {11d}

Clearly defining permitted and prohibited concomitant care is essential to preserving the integrity of its intervention, protecting participant health and minimising confounding factors.

Permitted concomitant care primarily includes recommendations for healthy visual habits, such as ensuring appropriate reading distance, adequate lighting, and regular outdoor activities. These practices are permitted and encouraged, as they align with standard myopia prevention guidelines.

In contrast, the following are strictly prohibited as concomitant care. First are alternative myopia control interventions. Participants are not allowed to use other myopia control strategies, such as atropine eye drops or other optical interventions (e.g., defocus lenses), during the trial period. Second are experimental therapies. Enrollment in other clinical trials or use of investigational devices or drugs targeting myopia management is prohibited to avoid confounding effects. Last but most important are device modifications. Any unauthorized adjustments or modifications to the DIST device or its usage protocol are also strictly prohibited.

To ensure adherence, all concomitant care received by participants must be reported to the research team and documented during follow-up visits. Any potential impact on study outcomes will be evaluated, and all such data will be recorded in the case report forms (CRFs). Participants and their families will be instructed to notify the study team of any changes in care or new treatments initiated during the trial.

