### Sample size {14}

To ensure adequate power for detecting differences in myopia incidence between the two intervention groups and the control group, we performed a sample size calculation based on historical data and statistical assumptions. Below, we outline the key parameters and methodological considerations underlying our determination.

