##### Alternative hypothesis (H_1_)

The incidence of myopia in the experimental (intervention) groups is lower than that in the control group.

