#### Type I error rate (alpha), power level (e.g., 80% power)

Type I error rate (α): 0.025/2 = 0.0125

Power (1-β): 80%

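### The protocol says the trial will evaluate synergy between DIST and optical defocus, but without a defocus-only arm it can answer only the package question and, without planned power, the add-on question

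*Protocol article*

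**What the plan says.** Two places promise synergy. Intervention description {11a} says the Combined Intervention group "evaluates the synergistic effect of combining DIST with an optical defocusing technique". The Discussion paragraph of the abstract says: "The study aims to determine the independent efficacy of DIST as well as its potential synergistic benefits when combined with optical defocusing techniques".

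Trial design {8} sets out the arms: "The three groups are no use of DIST, DIST alone (RIO-Max 2.0), and DIST optimized by combining the optical defocusing technique (RIO-Ultra 2.0"). They are "randomly divided into three groups of 64 subjects in a 1:1:1 ratio". The section on concomitant care {11d} closes off any other source of defocus data: "Participants are not allowed to use other myopia control strategies, such as atropine eye drops or other optical interventions (e.g., defocus lenses").

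The Sample size section {14} aims at "detecting differences in myopia incidence between the two intervention groups and the control group". The alternative hypothesis reads "The incidence of myopia in the experimental (intervention) groups is lower than that in the control group", and the error rate is given as "Type I error rate (α): 0.025/2 = 0.0125". One event rate, 21%, is given for the intervention group against 54% for control. The primary logistic model in Statistical methods {20a} lists study group as intervention against control.

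Other sections are more modest. Objectives {7} asks about the efficacy of DIST and of DIST integrated with defocus. The comparator rationale {6b} speaks of a possible enhancement, and the main Discussion asks whether the combination does better.

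**The concern.** Synergy means that the joint effect is larger than the two separate effects predict. To judge that, one must know what defocus does alone, and no arm shows it. The Background itself describes optical defocus as an established control strategy, so a benefit of the Combined arm over control could come largely or wholly from defocus.

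Two misreadings are at stake. A good Combined result could be reported as synergy. A non-significant Combined vs DIST result could be reported as no added value, although the trial was not sized for that comparison. The protocol expects its results to inform clinical recommendations, so the wording matters.

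**Working it through.** **1. Identifiability.** On the risk-difference scale the interaction is

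I = (p_Combined − p_DIST) − (p_defocus − p_control).

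The arms supply p_Combined, p_DIST and p_control. Nothing supplies p_defocus. As an illustration with assumed rates, take control 54%, DIST 30% and Combined 21%, so the first bracket is −0.09:

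- defocus alone 54% (no effect): I = −0.09 − 0 = −0.09, synergy;
- defocus alone 45%: I = −0.09 + 0.09 = 0, purely additive;
- defocus alone 21%: I = −0.09 + 0.33 = +0.24, less than additive.

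The same three observed rates fit all three conclusions. A larger sample would not separate them.

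**2. The plan's own sample size.** Inputs from the Sample size section: 0.54, 0.21, margin 0.05, α = 0.0125 (read as one-sided, since H1 is directional), power 80%, dropout 20%.

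n = [0.54×0.46 + 0.21×0.79] × (2.2414 + 0.8416)² / (0.54 − 0.21 − 0.05)² = 0.4143 × 9.505 / 0.0784 = 50.2, so 51 per arm; 51/0.80 = 63.75, so 64.

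This reproduces the stated figures of about 50 and 64. It is a calculation for one intervention arm against control. Splitting 0.025 in two matches two such comparisons and leaves nothing for a third.

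**3. Power for Combined vs DIST on myopia onset.** The protocol gives no separate rate for either device arm, so the rates below are assumptions. With no margin and two-sided 5%:

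power = Φ[(|p1 − p2| − 1.96·s0)/s1], where s0 = √(2p̄(1−p̄)/n) and s1 = √([p1(1−p1) + p2(1−p2)]/n).

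Example, 21% vs 10%, n = 51: p̄ = 0.155, s0 = 0.0717, s1 = 0.0708; (0.11 − 0.1405)/0.0708 = −0.43; Φ = 0.33.

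| DIST | Combined | n = 51 | n = 64 |
|---|---|---|---|
| 21% | 15% | 12% | 14% |
| 21% | 10% | 33% | 40% |
| 21% | 5% | 68% | 77% |
| 30% | 21% | 18% | 21% |
| 35% | 21% | 35% | 42% |
| 40% | 21% | 55% | 65% |
| 45% | 21% | 74% | 83% |

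The last column takes all 64 per arm as fully observed. With DIST at 21% and 51 per arm, 80% power needs a Combined rate of about 3%. For 80% power at 21% vs 10%, 169 per arm would be needed.

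**4. Precision.** If both arms are at 21%, the 95% half-width is 1.96 × √(2×0.21×0.79/51) = 0.158, about 16 points.

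**The case against.** The strongest reply is that this is one loose word in two places. The formal objective does not use it, and the package and add-on questions are ones that three randomised arms can estimate. That stands. A reader might infer that the trial's main aim fails, and the documents do not support this: the comparisons with control are untouched, and the separate DIST arm isolates DIST from control.

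Second, an active-versus-active contrast without power is common in three-arm trials and is not in itself an error. The protocol says openly what it was sized for, and exact contrasts may be left to an analysis plan that is not shown. It also signals comparison across all groups, through a trend analysis, a log-rank test among the three groups and p-values between intervention groups. This stands too. The lack of power is relevant only to how the result should be labelled. An analysis plan can supply the contrast but not the missing arm.

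Third, a reader might take the single 21% as a statement that the two devices are equally effective. It is a planning value, taken from a study of low-concentration atropine, for comparison with control. The table therefore varies either arm. Spherical equivalent and axial length may also be more sensitive to an add-on effect, but the protocol gives no standard deviations from which to compute power.

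Fourth, it is tempting to credit Combined vs DIST to the defocus function. The arms use different devices and the optical settings are not listed by device, so the contrast is between devices.

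The main Discussion admits that power may be insufficient, but it gives the lack of earlier studies as the reason. It mentions neither this contrast nor the missing arm.

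**Conclusion.** The synergy statements in the abstract and in Intervention description {11a} are wrong as written. This follows from the arms alone and rests on no assumed rate. What remains is the package question, sized as planned, and the add-on question, for which no power was planned. On myopia onset with 51 evaluable per arm, power for the add-on is 12% to 68% in one set of assumed rates and 18% to 74% in the other. Only the largest assumed difference (45% vs 21%) passes 80%, and only if all 64 per arm are observed. The point concerns what may be concluded and leaves the validity of the primary comparisons intact.

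**What to change.** Recruitment was completed in September 2025, so the remedy lies in wording and analysis:

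1. In the abstract and in {11a}, replace the synergy wording with *the added effect of the combined device (RIO-Ultra 2.0) over the DIST-only device (RIO-Max 2.0)*.
2. Fit study group with three levels. Report Combined vs DIST as a secondary contrast, as a risk difference with 95% confidence interval, labelled as not powered, and say that non-significance does not mean no added value.
3. State that Combined vs control estimates the whole package and shows neither synergy nor a DIST effect.

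The cost is a less favourable claim and one extra contrast from the same model. No new data are needed.

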**Fig. 2 Fig2:**
[figure not shown]
A schematic diagram of the optical path system. The blue lines represent the optical path for distant image display, and the red lines represent the optical path for defocusing intervention

Optical path parameters, such as the distance of the distant image, defocus magnitude, display resolution, and luminance at the eye, directly influence the experimental results. In this experiment, the distant image distance in the distant-image display pathway was set to 10 m, the defocus magnitude in the defocusing pathway was set to + 1.0 D, the display resolution was 1080p, and the luminance at the eye was set to approximately 150 nit.

This design enables a comprehensive evaluation of DIST’s efficacy both as a standalone intervention and in combination with optical defocus. By systematically comparing the outcomes across these groups, we aim to identify effective and practical strategies using DIST for delaying myopia onset. This evidence can directly inform clinical recommendations and public health strategies for myopia prevention. We recognize the potential for variability in participants’ adherence to the interventions. To mitigate this, detailed instructions will be provided, and adherence will be monitored through regular follow-ups.

